## Abstract

**Abstract:**

**Trial registration:**

*Registro Brasileiro de Ensaios Clinicos *(local acronym RBEC) [Internet]: Rio de Janeiro (RJ): *Instituto de Informaçao Cientifica e Tecnologica em Saude *(Brazil); 2010 - Identifier RBR-7dq5xx. Cross-sectional study on efficacy of negative expiratory pressure test proposed as screening for obstructive sleep apnea syndrome among commercial interstate bus drivers; 2011 May 31 [7 pages]. Available from http://www.ensaiosclinicos.gov.br/rg/RBR-7dq5xx/.

## Background

Sleep disorders are common throughout the world and have living effects on modern industrialized "24-hour" societies. The consequences of such disorders include excessive sleepiness, a negative effect on social and recreational activities, a decreased physical ability, a decline in productivity and a high risk of accidents [1]. These conditions, which are associated to acute or chronic insomnia, chronic sleep restriction, work shifts, jet lag, narcolepsy and obstructive sleep apnea (OSA), are a public health concern.

There is a large body of evidence demonstrating that sleepiness contributes toward industrial and traffic accidents [2]. It has previous been reported that 22% of accidents are caused by excessive sleepiness and 17-19% of traffic deaths are the result of sleepiness at the wheel [3]. The medical and economic costs of traffic accidents are estimated to be 1 to 3% of the gross domestic product of a country (annual cost of approximately 518 billion dollars). The *Instituto de Pesquisa Econômica Aplicada *(IPEA) [Institute of Applied Economic Research] of the Brazilian Federal Government reports that the mean cost of traffic accidents in Brazil is US$ 5,167,000, among which US$ 1,919.000 are spent on victimless accidents, US$ 2,942,000 are spent on accidents that result in injuries and US$ 2,476,000 are spent on accidents involving deaths [4].

OSA is a respiratory disease characterized by the collapse of the upper airways which occurs during sleep in predisposed subjects. Following chronic obstructive pulmonary disease and asthma, OSA is the epidemiological most important and widespread respiratory disease, affecting 3 to 7% of the male population and 2 to 5% of the female population between 40 and 65 years of age in the western world [5]. In Brazil, prevalence even larger was encountered according to an epidemiological study carried out in the city of Sao Paulo, where 24.8% males and 9.6% females were OSA patients [6].

One of the most important social implications of OSA is the increased risk for driving accidents [7]. Pack et al. (2002) reported a prevalence of 28% in a population of professional truck drivers [8]. The main cause of road accidents among professional drivers is lack of sleep, disturbance in the sleep/wake cycle (shift workers) and sleep disorders [9,10].

There is a close relationship between OSA and the risk of cardiovascular disease [11-13], neuropsychological problems [14,15], reduction in quality of life [16,17] and increase in the use of health resources [18,19], demonstrating that, when under-diagnosed, OSA can have serious consequences. Thus, the identification of new markers for OSA can be of considerable relevance for clinical practice.

An increase in the upper airway collapsibility is one of the main determinants of OSA [20,21]. Investigators have identified anatomical factors [22-24], neuromuscular control factors [25,26] and liquid and fat deposits [27] that may lead to increased pharyngeal collapsibility during sleep.

The negative expiratory pressure (NEP) method was initially used to assess intrathoracic expiratory flow limitations in patients with chronic obstructive pulmonary disease [28]. However, NEP test in individuals with OSA was found to lead to a collapse of the extrathoracic airway, with a drop in expiratory flow below the preceding expiration, which is common among patients with OSA [29-32]. The NEP test is carried out by administering negative pressure at the mouth during expiration. This maneuver is easy to perform and requires minimal patient cooperation. NEP test is based on the pressure gradient increase between the alveoli and open upper airway that results in an increase in expiratory flow. This study will allow the use of new screening technique to detect upper airway collapsibility, a high risk indicator for OSA in professional drivers. It's a daytime, low-cost screening method that could be included in a preventive strategy aimed at reducing the impact of this condition on accidents and the development of cardiovascular consequences.

### Objectives

The main objective of the study, which will be conducted on medium and long distance professional interstate bus drivers, is to investigate whether NEP test induced upper airway collapse is indicative for the presence and severity of OSA. Secondary objectives are: 1) identify the prevalence of OSA in this population; 2) determine the prevalence of metabolic syndrome and cardiovascular disease; 3) determine the correlation of work shift on clinical findings; and 4) validate a novel questionnaire on sleep quality proposed by the *Italian National Research Council Institute of Biomedicine and Molecular Immunology "A. Monroy" *and *Centro Medico di Veruno *(Italy).

## Methods/Design

### Study design

An observational, analytical study will be carried out at the Sleep Laboratory of the Master's and Doctoral Postgraduate Program in Rehabilitation Sciences of the Nove de Julho University (Brazil) (Figure 1). The design, conduction and reporting of this study will follow the norms of the "Standards for the Reporting of Diagnostic accuracy studies" - STARD statement.

**Figure 1 F1:**
[figure not shown]
**Design of the study**. Abbreviations: ESS - Epworth Sleepiness Scale; CNR - Consiglio Nazionale delle Ricerche; NEP - negative expiratory pressure.

### Subjects

Male professional bus drivers of an interstate roadway firm will be invited to participate in the study. The community-based sample includes shift workers: individuals working regular night shifts (from 10:00 pm to 08:00 am), individuals working regular day shifts (from 08:00 am to 06:00 pm), and subjects working rotating shifts.

With regard to the inclusion criteria, the sample will be made up by medium and long distance drivers, agreeing to participate in the study through a signed informed consent form. Subjects with acute pulmonary or heart disease and/or major cranio-facial or upper airway abnormalities, drug users and alcoholics will be excluded from the study.

### Protocol

The initial population of professional bus drivers includes 710 subjects. All will be asked to be part of the study and all procedures will be clarified. Those who agree to participate will undergo a detailed patient history, physical examination involving determination of blood pressure, anthropometric data, circumference measurements (hips, waist and neck), tonsils and Mallampati index. Moreover, specific questionnaires addressing sleep apnea and excessive daytime sleepiness will be administered. Data acquisition will be completely anonymous. Following the medical examination, the participants will perform a spirometry, NEP test and standard overnight polysomnography.

### Physical examination

Weight and height evaluation will be performed through an electronic balance (model 200/5, Welmy Industria e Comercio Ltda, Sao Paulo, Brazil) and body mass index (BMI) will be calculated [33]. For the assessments of tonsils and Mallampati index, subjects will be in the sitting position and instructed to open the mouth as much as possible [34,35].

Waist circumference will be measured with the subject in the upright position, standing at the midpoint between the costal margin and the iliac crest at the end of normal expiration. The hip circumference will be measured with the subject in the same position at the level of the greater trochanter. Neck circumference will be measured with the subject in the sitting position at the edge of the cricoid cartilage.

### OSA and excessive daytime sleepiness questionnaires

The Berlin Questionnaire will be administered. This 10-item questionnaire has recognized efficacy in distinguishing subjects at greater risk for OSA in primary care population [36]. The Epworth Sleepiness Scale [37] will be used for the assessment of excessive daytime sleepiness. Moreover, a novel OSA questionnaire designed by researchers of the Italian National Research Council - Institute of Biomedicine and Molecular Immunology "A. Monroy" and Centro Medico di Veruno will be administered.

### Spirometry

The spirometry will be carried out during the day, with the patient seated in a comfortable position. For such, the KoKo PFT System Version 4.11 (nSpire Health, Inc; Louisville, CO, USA) will be used following national guidelines for the execution of lung function tests by the Brazilian Society of Pneumology [38] and the European Respiratory Society [39]. The subjects will perform the test in a comfortable position, with the body erect and the upper limbs unsupported. All examinations will be carried out by a competent technician trained in obtaining the necessary cooperation from the subjects and appropriately operating the equipment in order to ensure accurate, reproducible results. The equipment will be calibrated prior to each exam with a 3-L syringe [38].

### Negative expiratory pressure - NEP test

The NEP test is performed through the administration of negative pressure at the mouth during expiration. This is a practical test performed while awake and requires little cooperation from the subject. In the absence of expiratory flow limitation, the increase in the pressure gradient between the alveoli and open upper airway caused by NEP results in an increase in expiratory flow.

NEP will be generated by a Super Air Amplifier (Exair model 120021 Cincinnati, Ohio, USA) coupled to a tank of compressed air via an electrically operated solenoid valve (Norgren Ltd model 95004; Vimercate, MI, Italy) automatically activated in early expiration and kept open for 2 s by software control (Figure 2). A pneumotachograph (Hans Rudolph model 3830; Kansas City, MO, USA) will be connected to the air amplifier and the mouthpiece to measure airflow ($\dot{\text{V}}$) with pressure transducers (PCLA02X5; Sensortechnics GmbH, Puchheim, Germany). Mouth pressure will be measured by pressure transducers (PCLA0050; Sensortechnics GmbH, Puchheim, Germany). NEP of 10 cm H_2_O will be set by occluding the pneumotachograph with a stopper and adjusting the flow of compressed air to air amplifier (Figure 2).

**Figure 2 F2:**
[figure not shown]
**Schematic representation of the negative expiratory pressure apparatus**.

NEP maneuvers will be performed (each after at least four breaths to normalize the breathing pattern). The tests will be carried out once with the subjects seated comfortably and one other in supine position on a cot. In both positions, care will be taken to maintain the subjects comfortable with the neck in a neutral position, as it has been documented that the position of the head exerts an influence over upper airway collapsibility [40]. All maneuvers will be performed with the subjects awake and wearing a nose clip. The airflow and the mouth pressure signals will be low-pass filtered and sampled at 200 Hz. Both digital signals will be displayed in real time on the monitor and stored on the computer for subsequent analysis. Signal analysis and solenoid valve control will be performed using software written in Labview 8.2 (National Instruments) developed by the Italian National Research Council, Institute of Biomedicine and Molecular Immunology "A. Monroy".

NEP application during tidal expiration produces an immediate peak flow followed by a sudden drop of a variable degree. Upper airway collapsibility is evaluated by measuring flow limitation as flow drop (Δ$\dot{\text{V}}$), expressed as the percentage of peak flow immediately after NEP administration. To avoid reflex and voluntary reactions to the NEP stimulus, the minimal flow will be identified in the first 200 ms of NEP administration [41]. Upper airway collapsibility is also evaluated by measuring V_0.2 _immediately after NEP administration (Figure 3). These values are expressed as the percentage of mean inspiratory volume of the three breaths preceding NEP administration. Measured volumes are accepted only when differences between inspiration and expiration for each of the three previous breaths are less than 10%. Values of V_0.2 _and Δ$\dot{\text{V}}$ (%) are calculated as the mean of four measurements.

**Figure 3 F3:**
[figure not shown]
**Measurements techniques for upper airway collapsibility evaluated as expiratory volume in 0.2s (V_0.2 _- percent of the mean inspiratory volume of the three breaths preceding NEP application) and as the flow drop (Δ$\dot{\text{V}}$- expressed as the percent of the peak flow)**.

### Standard overnight polysomnography

Nocturnal polysomnography will be carried out using the Embla Somnologica Studio - EMBLA A10, version 3.1.2. (Flaga hf. Medical Devices, Iceland) sleep analysis system. The following signals will be recorded: electroencephalogram (F4-M1, C4-M1, O2-M1, and backup electrodes F3, C3, O1 and M2), electrooculograms (E1-M2, E2-M2), chin and tibials electromyography, electrocardiogram, oxygen saturation, pulse rate, oronasal airflow (nasal canula and thermistor), respiratory effort (thoracic and abdominal Xtrace model straps), snoring, and body position. The patients will be instructed to remain relaxed and sleep naturally as at home. Throughout the night, the subjects will be monitored by a technician experienced in polysomnography [42]. The reading will be performed by professionals who were blinded to the result of the NEP test, following the guidelines of the American Academy of Sleep Medicine [43] and criteria of the Brazilian Sleep Society.

Apneas are defined as lack of airflow or a reduction ≥90% in the airflow signal for at least 10 s. Hypopneas are defined as discernible drop in flow by ≥ 30% of baseline for a period lasting at least 10 s followed by a SaO_2 _fall ≥4%. AHI will be calculated as number of (apneas + hypopneas)/h of total sleep time. Subjects with AHI ≥5 will be classified as OSA [42,43].

### Quality control

In order to ensure data quality, the physiotherapists and physicians in charge of data collection will receive specific training. Periodic external monitoring will be performed to verify adequate application of methodology in performing examinations and data collection.

### Calculation of sample size and statistical analysis

The calculation of sample size was based on the correlation reported by Insalaco et al. [44] between Δ$\dot{\text{V}}$(%) and AHI in patients with OSA (r = 0.37). For a bidirectional alpha value of 0.05 and 90% power, a minimum number of 82 subjects will be necessary.

Kolmogorov-Smirnov normality test will first be performed in order to determine the presence or absence of a normal distribution sample. Descriptive analysis will be performed, with the data expressed as either mean and standard deviation or median values and 95% confidence intervals, when appropriate. One-way analysis of variance (ANOVA) will be used for comparisons between work shifts once the samples have a normal distribution. V_0.2 _and Δ$\dot{\text{V}}$(%) values will be linearly correlated with the AHI, for which either Pearson's or Spearman's correlation test will be used, depending on the sample distribution. Either the non-paired Student's t-test or Mann-Whitney test will be used for comparisons between individuals with and without OSA. Logistic regression for the analysis of continuous factors with categorical responses will be performed. Receiver operating characteristic (ROC) curves will be constructed to determine the sensitivity (true positive rate) versus 100-specificity (false positive rate) at various levels of the measured Δ$\dot{\text{V}}$ (%) and V_0.2 _(%) to identify the cut-off value yielding the largest number of correctly classified patients. The statistical analysis will be performed by an experienced statistician using the JMP commercial program (version 8.0, SAS Institute Inc.) and SPSS program (version 16.0, Somers NY). A 5% level of significance and 95% confidence interval will be applied.

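### The 90% power for 82 subjects rests on a correlation seen only within OSA patients, so it is unsupported for the unselected drivers enrolled and does not cover the diagnostic (ROC) aim

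*Protocol article*

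**What the plan says.** In the protocol article, Calculation of sample size and statistical analysis takes its planning value from an earlier study's correlation of flow drop "and AHI in patients with OSA (r = 0.37". It concludes: "For a bidirectional alpha value of 0.05 and 90% power, a minimum number of 82 subjects will be necessary". It states no other planning quantity: no AUC, sensitivity, specificity, number of OSA cases or precision.

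The people enrolled are defined differently. Under Subjects, "Male professional bus drivers of an interstate roadway firm will be invited to participate in the study", and no criterion selects for OSA. Under Protocol, "The initial population of professional bus drivers includes 710 subjects", and all of them are to be asked to take part.

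Under Objectives, the main aim is to "investigate whether NEP test induced upper airway collapse is indicative for the presence and severity of OSA". The Discussion describes the purpose as deciding whether the test can serve for screening. The analysis text correlates V0.2 and flow drop with AHI, without limiting this to OSA cases, and plans ROC curves to choose a cut-off.

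The Background cites three prevalences that bear on men or on drivers: a Sao Paulo survey "where 24.8% males and 9.6% females were OSA patients", a study that "reported a prevalence of 28% in a population of professional truck drivers", and a general figure for ages 40 to 65 "affecting 3 to 7% of the male population".

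**The concern.** Two links are missing between the planning value and the study.

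- **Population.** A correlation within OSA patients describes people who all have AHI of at least 5. The drivers will include many below that threshold if the cited prevalences are any guide. Adding them changes the spread of AHI and the shape of the relation, and r can move either way. The article neither argues that 0.37 carries over nor says that it is assumed to.
- **Question.** A test of r = 0 asks whether flow drop and AHI are associated. It does not ask whether a cut-off separates drivers with and without OSA well enough for screening. That depends on the numbers of cases and non-cases and on the precision of sensitivity, specificity and AUC.

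The risk is that readers take 82 subjects and 90% power as backing for the screening conclusion, which the calculation never addressed.

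**Working it through.** **1. The plan's own figure.** Inputs from the sample-size paragraph: r = 0.37, two-sided alpha 0.05, power 90%.

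Fisher z: N = ((1.960 + 1.282)/atanh(0.37))² + 3, with atanh(0.37) = 0.3884.
N = (3.242/0.3884)² + 3 = 72.6, so **73, not 82**.

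Other standard methods at two-sided 5% and 90% power (bias-corrected Fisher z, noncentral t, Spearman adjustments) give 69 to 80. The figure 82 would follow from r = 0.35 (81.7) or from a 10% loss allowance (73/0.90 = 81.1, rounded up), but the article states neither. At r = 0.37, 82 subjects have 93% power.

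**2. Power of the planned all-driver correlation with 82 drivers.** Power = Φ(√(n − 3) × atanh(r) − 1.960), with n = 82 and √79 = 8.888. The whole-sample r is not in the document, so these values are assumptions.

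| Assumed r, all drivers | Power |
|---|---|
| 0.20 | 44% |
| 0.25 | 62% |
| 0.30 | 79% |
| 0.37 | 93% |
| 0.50 | over 99% |

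**3. OSA cases if exactly 82 enrol.**
- At 24.8%: 82 × 0.248 = 20.3.
- At 28%: 82 × 0.28 = 23.0.
- At 3 to 7%: 82 × 0.03 = 2.5 to 82 × 0.07 = 5.7.

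**4. Power for r = 0.37 in the population it came from.** This within-OSA analysis is not specified in the plan.
- n = 20: Φ(√17 × 0.3884 − 1.960) = Φ(−0.36) = 36%.
- n = 23: Φ(√20 × 0.3884 − 1.960) = Φ(−0.22) = 41%.

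Simulation of bivariate normal data gave 37% and 42%. Reaching 73 OSA cases would take 73/0.28 = 261 to 73/0.248 = 295 drivers (rounded up), which is 37% to 42% of the 710 invited.

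**5. Diagnostic precision with 23 cases and 59 non-cases** (82 drivers at 28%). The accuracy values are assumed for illustration; the article gives none.
- Sensitivity 18/23 = 78%: Wilson 95% CI 58% to 90%.
- Specificity 47/59 = 80%: Wilson 95% CI 68% to 88%.
- AUC 0.70, Hanley-McNeil: Q₁ = 0.70/1.30 = 0.538 and Q₂ = 2 × 0.49/1.70 = 0.576. Variance = (0.21 + 22 × 0.0485 + 58 × 0.0865)/(23 × 59) = 0.0046. SE = 0.068, so ±0.13.

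**The case against.** The best defence is that the design may well be adequate, and much of it stands.

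- **The planned correlation uses all drivers.** A reader might infer from step 4 that the study has only 36-41% power. The document does not support that, because the analysis text does not restrict the correlation to OSA cases. For the all-driver test, power could exceed 90%. It is unsupported, not shown to be low.
- **82 is a minimum.** A reader might infer that sensitivity will be estimated from about 20 cases. That holds only at the floor. All 710 drivers are invited, and full uptake would give about 710 × 0.248 = 176 to 710 × 0.28 = 199 cases. On the other side, 82 is the only number the article commits to.
- **The prevalences are borrowed.** They come from other populations, the lower range of 3 to 7% is also cited, and prevalence in these drivers is itself a secondary objective. The count of 20-23 is therefore an assumption.
- **Correlation with AHI does address severity.** It would be too strong to say that the power calculation is irrelevant to the main objective, since severity is half of it.
- **Some discrimination could be shown even at the floor.** An AUC of 0.70 ± 0.13 excludes 0.5. That would show the test is better than chance, but would not fix a usable screening cut-off.

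One could add that diagnostic precision belongs in a fuller document. The point here is different: the article itself states a power figure whose basis matches neither its population nor the diagnostic half of its aim.

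**Conclusion.** The point holds in a limited form. The mismatch is plain on the page: a within-OSA correlation is used to size a study of drivers unselected for OSA, and nothing in the calculation concerns the presence of OSA or the ROC cut-off. The stated 90% is therefore unsupported for the planned correlation and does not apply to the screening conclusion. Its true value depends on a whole-sample r that the document does not give.

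The wide diagnostic intervals depend on three assumptions: enrolment stopping at 82, prevalence near 28%, and the illustrative accuracy values.

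Separately, 82 does not follow from the stated inputs. That discrepancy is on the conservative side and does not repair the mismatch. Confidence is high for the mismatch and for the figure of 73. No actual shortfall in power has been demonstrated. The paragraph should be restated.

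**What to change.** Restate the sample-size paragraph in three respects.

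1. Say that r = 0.37 was reported within OSA patients and is assumed to hold across all enrolled drivers. On that assumption 82 subjects give about 93% power and 73 give 90%; otherwise name the input that yields 82. Show power over a range of r, as in the table above.
2. Give the expected numbers with and without OSA among 82, and the resulting 95% CI widths for sensitivity, specificity and AUC, with prevalence and accuracy labelled as assumptions. Say that the 90% power does not apply to the diagnostic conclusion.
3. State that 82 is a floor and that all consenting eligible drivers among the 710 invited will be tested, as the Protocol section already implies.

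The cost is rewording one paragraph, with no new procedure or visit. The drawback is that the stated power becomes conditional and looks less favourable.

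### The only analysis named for the work-shift objective is an unadjusted one-way ANOVA that depends on normality, which leaves it open to confounding and probably leaves AHI without a named shift test

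*Protocol article*

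**What the plan says.** The protocol article lists as its third secondary objective to "determine the correlation of work shift on clinical findings". It does not list which findings are meant. Under Subjects it says "The community-based sample includes shift workers" and describes three existing work patterns: regular night, regular day and rotating. Study design calls the study observational.

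The section on sample size and statistical analysis opens with a distribution check: "Kolmogorov-Smirnov normality test will first be performed in order to determine the presence or absence of a normal distribution sample". For shift it then says "One-way analysis of variance (ANOVA) will be used for comparisons between work shifts once the samples have a normal distribution". It names no covariate and no alternative test for this comparison. The two neighbouring comparisons each have a rank-based alternative. For the NEP measures against AHI, "either Pearson's or Spearman's correlation test will be used, depending on the sample distribution". For drivers with and without OSA, "Either the non-paired Student's t-test or Mann-Whitney test will be used for comparisons between individuals with and without OSA". The only regression model in the section is "Logistic regression for the analysis of continuous factors with categorical responses will be performed".

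BMI and the waist, hip and neck circumferences are collected (Protocol; Physical examination). Age is not listed by name, but a detailed history is taken. The Discussion treats obesity as an important predictor of OSA.

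**The concern.** There are two separate problems.

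First, a one-way ANOVA has one factor and no covariates. Shift is a feature of each driver's working life and is not assigned by the study. If drivers on one shift are older or heavier, a difference in AHI, blood pressure or sleepiness that follows from age or weight will appear as a difference between shifts. Larger samples do not cure this. They make the spurious difference easier to detect, and 710 drivers are to be invited.

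Second, the ANOVA is to be run only if the data are normal, and nothing is named for the other case. AHI counts events per hour of sleep and cannot fall below zero. In a working population that includes many drivers without OSA, a right-skewed distribution is likely. The main sleep outcome may then reach the shift comparison with no prespecified test, and the choice would be made after the data are seen.

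**Working it through.** **The plan's own figure.** None is given for the shift comparison. The stated minimum of 82 belongs to the correlation of flow drop with AHI (r = 0.37, two-sided 5%, 90% power). The Fisher z formula gives ((1.960 + 1.282)/atanh 0.37)² + 3 = 72.6, so 73. The difference from 82 is a separate matter. Here 82 serves only as the stated minimum n.

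**Does another sentence cover the objective?**
- The logistic regression sentence is for continuous factors with categorical responses. Shift is a categorical factor and AHI a continuous response, so as worded it does not apply.
- The Spearman and Mann-Whitney alternatives belong to other comparisons. Neither compares three shifts.

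**Size of the confounding risk.** All inputs except n are assumptions:
- three equal shift groups and no true shift effect;
- one shift higher by d SD in a covariate;
- within-shift correlation ρ between covariate and outcome, with outcome SD 1.

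One group mean is then displaced by ρd. The ANOVA F statistic is noncentral with λ = n(ρd)² × (1/3)(2/3), on 2 and n − 3 degrees of freedom. At n = 82 the critical value is 3.11.

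| d (SD) | ρ | λ at n = 82 | Rejection rate |
|---|---|---|---|
| 0 | any | 0 | 5% |
| 0.25 | 0.3 | 82 × 0.005625 × 2/9 = 0.10 | 5.8% |
| 0.25 | 0.5 | 82 × 0.015625 × 2/9 = 0.28 | 7.1% |
| 0.5 | 0.3 | 82 × 0.0225 × 2/9 = 0.41 | 8.1% |
| 0.5 | 0.5 | 82 × 0.0625 × 2/9 = 1.14 | 14.1% |
| 1.0 | 0.3 | 82 × 0.09 × 2/9 = 1.64 | 18.6% |
| 1.0 | 0.5 | 82 × 0.25 × 2/9 = 4.56 | 45.0% |

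Simulation of the same set-up gave 5 to 7% at 0.25 SD and 8 to 44% over 0.5 to 1.0 SD, which agrees within simulation error.

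The rate grows with n. A second simulation used a milder pattern, with covariate means 0, d/2 and d across shifts. For d = 0.25 to 0.5 SD it gave 4 to 12% at n = 82, 6 to 34% at n = 300 and 10 to 67% at n = 710. Adjusting for the covariate kept the rate at about 4 to 6% throughout.

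**The normality condition.** Assume log-normal AHI with log-SD 0.8 to 1.2. A Kolmogorov-Smirnov test with estimated mean and SD, applied to all 82 subjects, rejects normality in about 86 to 99.9% of samples. The shift comparison of AHI would then have no named test.

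The text does not say whether the check is pooled or made within each shift, or which version is used. With 27 drivers per shift and log-SD 1:
- the uncorrected test detects the skew in about 34 to 36% of samples per shift;
- it flags at least one of three shifts in 1 − 0.64³ = 74%;
- with the Lilliefors correction, detection per shift is about 88 to 90%.

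So the condition fails under most readings of the text.

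**The case against.** The objective is secondary and can be read as descriptive, and a crude comparison does answer a descriptive question. An article may also leave covariate sets and a fallback test to a fuller document. On the fallback alone this has force, since most analysts would use Kruskal-Wallis without being told. It has less force on the method. The article does not leave that open: it names a single-factor test for non-allocated groups, while supplying alternatives for the neighbouring comparisons at the same level of detail.

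Three stronger readings are tempting and should not be drawn.

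- A reader might infer that shift is confounded with age and BMI. The article gives neither by shift, and only a risk is supported. With no imbalance there is no inflation, and at 0.25 SD and n = 82 there is almost none.
- A reader might infer that the Kolmogorov-Smirnov check usually misses skewed AHI, so that ANOVA would be run on it regardless. That needs an uncorrected test judged separately within each small shift group. Even if ANOVA were run on such data, its simulated type I error was 3.9%, so skew would not produce false positives.
- A reader might infer that AHI has no rank-based analysis anywhere. The gap is confined to the shift comparison.

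Adjusting for BMI as a matter of course is also open to objection. Shift work may itself affect weight, so BMI may lie on the path from shift to OSA, and it is close to some of the clinical findings.

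**Conclusion.** The point holds as a moderate one on a secondary objective. The main NEP analysis is unaffected. It follows from the text that the sole analysis named for work shift is unadjusted, depends on normality and has no stated alternative. The consequences are conditional. A false-positive rate of about 8 to 44% at n = 82 requires an imbalance of 0.5 to 1.0 SD in one shift and a covariate-outcome correlation of 0.3 to 0.5. The rate is about 5 to 7% at 0.25 SD, and higher for a given imbalance in a larger sample. That AHI would usually be left without a named shift test rests on assumed log-normal skew and, at its strongest, on a check pooled over all subjects.

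**What to change.** Replace the ANOVA sentence with wording to this effect:

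*Clinical findings will be compared across night, day and rotating shifts by regression with shift as a three-level factor, adjusted for age: linear regression for continuous findings and logistic regression for binary ones. No normality test will decide whether the comparison is made. AHI will be analysed as log(AHI + 1). A further model will add BMI for outcomes that are not themselves measures of obesity, with the caution that BMI may be a mediator. Unadjusted comparisons will be reported alongside and described as descriptive.*

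A rank-based test such as Kruskal-Wallis is an acceptable alternative for AHI. It closes the distributional gap but does not adjust for age, so it belongs with the descriptive comparison.

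The cost is small. Shift uses two degrees of freedom, as it does in the ANOVA; age as a linear term adds one, and BMI one more in the further model. BMI is already collected. Age should be available from the history and needs only to be confirmed as a recorded item. There is slightly more analysis to run and report.
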